**Figure 1 Fig1:**
[figure not shown]
**Registry design.**

### Data collection

Patient data will be collected using electronic case report forms (eCRFs), which must be signed electronically by investigators and/or designees (Table 1). The eCRFs should be completed at the earliest opportunity. All registry documents will identify subjects by patient registry identification numbers only (or initials when applicable).

**Table 1 Tab1:** **Data collection**

Parameter	Admission	Intervention	Discharge	30d FU	6 Mo FU
Inclusion/Exclusion criteria	X				
Demographics	X				
Diagnosis of valve disease	X				
Echocardiography	X				
Symptoms	X			X	X
Cardiac baseline characteristics	X				
ECG	X		X		
Comorbidities	X				
Risk scores	X				
Prior cardiovascular intervention	X				
Current medications	X		X	X	X
Interventional details		X			
Interventional results		X			
AE		X	X	X	X
Hospitalization duration			X		
Creatinine value	X		X		
Early safety/Clinical efficacy				X	X

A total of 20% of the sites (i.e., up to two sites) will be selected at random for monitoring following completion of patient follow-up and documentation. Source data verification will be performed for all patients in these centers. Also, 100% source data verification will be conducted for the following serious adverse events: death, stroke, major bleeding, valve complications, vascular complications, permanent pacemaker implantation, and renal failure. For data analysis, linearized rates and actuarial probability statistics will be used for adverse event reporting, and Kaplan-Meier analyses will be performed for survival and adverse event outcomes when appropriate.

### Statistics

The sample size for EASE-IT was established based on previously reported event rates and the feasibility to detect an absolute risk reduction for the primary endpoint of 13% at 30 days while taking into consideration a 10% drop out rate [18, 20]. Intention-to-treat analysis, based on all patients enrolled in the registry will be performed. Subjects are considered registry participants when they enter the cath lab/hybrid suite. Descriptive data summaries will be used to present and summarize the collected evaluation data. For categorical variables (e.g. gender) frequency distributions will be given. For numeric variables (e.g. patient age) minimum, maximum, mean, median and standard deviation will be calculated. Linearized rates and actuarial probability statistics may be used where appropriate for adverse event reporting. Kaplan-Meier analysis will be performed for survival outcomes and where appropriate for adverse event outcomes.

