### Methods/Design of EASE-IT

EASE-IT is a multicenter, prospective, two-armed, observational registry. Enrollment of 200 subjects will take place at up to 10 study-sites in Germany. Approval was obtained by the Ethics Committee of the Landesärztekammer Stuttgart on February 25^th^ 2014 and confirmation obtained at each site participating in ROUTE prior to patient enrollment. All patients are required to provide written informed consent prior to participation. The investigation commenced in April 2014.

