### Patient selection

Patient eligibility for EASE-IT will be based on the following criteria: (1) indication for TAVI in accordance with the Edwards SAPIEN 3 instructions; (2) eligibility for TAVI with and without BAV; and (3) at least 18 years of age. Patients with contraindications based on instructions for use of either TAVI or the Ascendra Balloon Catheter will be excluded from the study. Additionally, patients meeting any of the following criteria will be excluded: (1) logistic EuroSCORE I >50%; (2) mitral or tricuspid valvular insufficiency (> grade II); (3) previous aortic valve replacement; (4) uncontrolled atrial fibrillation; (5) left ventricular or atrial thrombus by echocardiography; (6) recent cerebrovascular event (within the last 3 months);and (7) high probability of non-adherence to follow-up requirements (due to social, psychological, or medical reasons). Each participating center must document 10 consecutive cases with BAV and 10 cases without BAV.

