### Procedure

Notably, TA-TAVI with pre-dilation is to be performed as previously described by Walther et al. [13], whereas the procedure without pre-dilation will be carried out in a similar manner to that described by Wendler et al. [20]. Pre-operation computed tomography will generally be used for valve sizing purposes. However, investigators can modify these procedures to fit their needs. Patients will be assigned into groups (i.e., with BAV or without BAV) by their physician prior to study enrollment and independent of the registry.

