### Pre-defined objectives

The primary evaluation criteria at 1 month will consider the combined endpoint of all-cause mortality, stroke, non-fatal myocardial infarction, acute kidney injury, and pacemaker implantation within 30 days after TAVI as to VARC2 (Figure 1). Secondarily, the rates of each of these individual adverse events will be considered, along with duration of radiation, amount of contrast agent, and aortic root rupture. Six months after TAVI, the combined and separate adverse events will once again be evaluated. Patient outcomes will be compared between the two groups, with implantation plus pre-dilation considered as the control arm.

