## Discussion

EASE-IT represents a prospective, multicenter, two-armed registry aimed at documenting the course of patients undergoing TA-TAVI using the Edwards SAPIEN 3 with or without pre-dilation via BAV. Information provided by EASE-IT will be used to assess the value of pre-dilation during TAVI procedures and to investigate associations between patient characteristics and outcomes. Thus, results obtained from the EASE-IT registry should have several important implications.

Although recent pilot studies have preliminarily suggested the feasibility and safety of performing TF-and TA-TAVI without pre-dilation of the stenosed aortic valve [18–20], these studies have not directly compared the outcome of patients undergoing TAVI with and without pre-dilation. Nevertheless, in the study by Grube et al. [18], 60 subjects undergoing TF-TAVI using the MCV device in the absence of BAV were compared to a historical control group (with BAV), suggesting that the efficacy of the simplified procedure (i.e., without pre-dilation) was similar to that of the standard approach. However, it is known that this type of comparison can be associated with several methodological limitations. Therefore, the conclusions by Grube et al. must be appropriately verified. In addition, data regarding delivery of the Edwards SAPIEN THV in the absence of pre-dilation are extremely limited [20]. For these reasons, EASE-IT has been designed to determine whether BAV during TA-TAVI using the Edwards SAPIEN 3 yields relevant beneficial or negative procedural effects based on a two-armed registry approach, which will allow for direct comparison between the patient groups (i.e., with BAV *vs.* without BAV). Thus, the comparative analysis that can be performed from information collected during the EASE-IT registry will be fundamental for establishing the importance of pre-dilation during TA-TAVI.

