### Potential limitations of EASE-IT

Although EASE-IT represents a critical step for examining the importance of performing pre-dilation during TAVI procedures involving Edwards SAPIEN 3, the study might display limitations related to its design. Indeed, the non-randomized nature of the registry could lead to potential bias, as investigators will assign patients into the “with BAV” and “without BAV” groups at their discretion while patients are eligible for either route. In addition, because we ask for patients eligible in principal for TAVI with AND without BAV we will miss those only eligible for one of the routes. This cannot be avoided, however, if we want to compare both techniques in one patient population. We have chosen to use the observational design because we only incompletely know the variables affecting the decision and are thus not able, without a pilot documentation like the present one, to properly assess the variables necessary for the decision and these might deserve a prospective assessment in an upcoming randomized controlled trials.

Nevertheless, inclusion into the EASE-IT trial requires that patients be eligible for TAVI with and without BAV, which could alleviate the potential for bias. In addition, registry data tend to be less complete when compared to randomized clinical trials. However, in this regard, 20% of the sites will be randomly selected for monitoring following completion of patient follow-up and documentation. Source data verification will be performed for all patients in these centers. Moreover, it is possible that the 6-month follow-up will not be sufficient to detect differences in long-term adverse outcomes between the groups with and without pre-dilation. Thus, future randomized clinical trials may be needed in order to assess the long-term effects associated with eliminating BAV from the TA-TAVI procedure.

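### Physicians choose the arm but every analysis the article names is unadjusted, so the 30-day comparison of no BAV with BAV is open to confounding of unknown size and direction

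*Protocol article*

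**What the plan says.** **Allocation.** The Procedure section states: "Patients will be assigned into groups (i.e., with BAV or without BAV) by their physician prior to study enrollment and independent of the registry". The limitations section repeats that investigators assign at will among patients who could receive either technique.

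**Comparison.** Under Pre-defined objectives, the primary criterion is the "combined endpoint of all-cause mortality, stroke, non-fatal myocardial infarction, acute kidney injury, and pacemaker implantation within 30 days after TAVI". The same section adds: "Patient outcomes will be compared between the two groups, with implantation plus pre-dilation considered as the control arm". The Statistics section sizes the registry to detect a 13-point absolute reduction in this endpoint.

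**Analysis.** The Statistics section names an intention-to-treat set of all enrolled patients and states: "Descriptive data summaries will be used to present and summarize the collected evaluation data". It specifies frequency distributions for categorical variables and minimum, maximum, mean, median and standard deviation for numeric ones. Linearized and actuarial rates are optional for adverse events, and Kaplan-Meier analysis is planned for survival and, where suitable, for adverse events. The Data collection section repeats the last two items.

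**Mitigation.** The limitations section concedes that non-randomised assignment may bias the result and that the determinants of the choice are only partly known. Against this it offers eligibility for both techniques, "which could alleviate the potential for bias".

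**Use of the result.** The Discussion says the comparative analysis "will be fundamental for establishing the importance of pre-dilation during TA-TAVI". It goes on to consider dropping the pre-dilation step if the registry shows it to be unnecessary or harmful.

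**The concern.** The registry sets out a controlled comparison with a target effect, but the arms are formed by clinical judgement. When the reasons for the choice also predict death, stroke, myocardial infarction, kidney injury or pacemaker implantation, the crude difference between arms combines the effect of BAV with the risk profile of the patients selected for it.

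The article itself points to one plausible reason. Its Discussion reports a suggestion that omitting BAV suits patients with severely impaired left ventricular ejection fraction (LVEF). If physicians act on that, and if low LVEF raises the 30-day risk, the no-BAV arm would look worse than it should. A habit of sending higher-risk patients to BAV would make the no-BAV arm look better than it should. Neither the crude summaries nor the Kaplan-Meier curves could tell these situations from a true effect, or from its absence.

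At stake is the main result of the registry and the practice conclusion that the Discussion intends to draw from it.

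**Working it through.** **1. The design figures.** The article states "Enrollment of 200 subjects will take place at up to 10 study-sites in Germany" and "Each participating center must document 10 consecutive cases with BAV and 10 cases without BAV". Ten sites × 20 patients = 200, so the total agrees with a 1:1 quota. After the stated 10% dropout, 200 × 0.90 = 180, or 90 per arm. The power calculation behind 200 cannot be reproduced, because control event rate, alpha, sidedness and power are not given. This point does not depend on it.

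**2. Does any named method adjust for selection?**

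| Item named in the article | Adjusts for patient selection? |
|---|---|
| Intention-to-treat set | No; it fixes who is analysed |
| Descriptive summaries | No |
| Linearized and actuarial rates | No |
| Kaplan-Meier | No |
| Associations of patient characteristics with outcome | An aim without a stated method, not linked to the BAV comparison |
| Eligibility for both techniques | Supports positivity (each patient could receive either), not exchangeability of those chosen |
| 10 + 10 quota per site | Balances centre between arms if met; does not balance patient risk within a centre |

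**3. How large could the distortion be?** The article gives no event rates or imbalances, so all risks and prevalences below are assumptions. Take one binary prognostic factor, no true BAV effect and 90 per arm.

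- Spurious difference: d = (prevalence in one arm − prevalence in the other) × (risk with factor − risk without).
- Standard error: SE = √[2p(1 − p)/90], where p is the mean risk of the two arms.
- Rejection rate of a crude two-sided 5% test: Φ(−1.96 + d/SE) + Φ(−1.96 − d/SE).

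| Prevalence | Risk with / without | d | p | SE | d/SE | Rejection |
|---|---|---|---|---|---|---|
| 60% vs 40% | 35% / 15% | 0.20 × 0.20 = 4.0 points | 25% | 6.45 points | 0.62 | 9.5% |
| 65% vs 35% | 35% / 15% | 0.30 × 0.20 = 6.0 points | 25% | 6.45 points | 0.93 | 15.3% |
| 65% vs 35% | 40% / 15% | 0.30 × 0.25 = 7.5 points | 27.5% | 6.66 points | 1.13 | 20.3% |

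Against the 13-point target, 4.0/13 = 31% and 7.5/13 = 58%.

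**4. Sensitivity to a lower event rate.** Keep the risk ratios of the first and third rows, but lower the risk without the factor to 10%.

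- 60% vs 40%, ratio 35/15: risk with the factor 23.3%, d = 0.20 × 13.3 = 2.7 points, p = 16.7%, SE = 5.56 points, rejection 7.7%.
- 65% vs 35%, ratio 40/15: risk with the factor 26.7%, d = 0.30 × 16.7 = 5.0 points, p = 18.3%, SE = 5.77 points, rejection 14.0%.

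The distortion is smaller at lower risk, but the rejection rate remains above the nominal 5%.

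**The case against.** The strongest reply is that this is a condensed article. Covariate sets and propensity models are commonly left to a full protocol or analysis plan, which may exist and may contain them. No sentence excludes adjustment. The authors disclose the bias, give it as the reason for an observational design, and describe the registry as pilot work ahead of a randomised trial.

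Much of this stands, and it limits the point. A reader might infer more than the article supports in these ways:

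- **That the comparison is confounded in a known direction, by LVEF, calcification or frailty.** Only LVEF is tied to the BAV decision in the text, and the authors say they know the drivers incompletely.
- **That an invalid test or confidence interval is prescribed.** The article specifies neither. The rejection rates above describe what a crude test would do if one were run.
- **That centre is neglected.** The quota, if met, already balances centre between arms. Accounting for it mainly respects the design and helps precision.
- **That the authors claim eligibility removes the bias.** They say only that it could reduce it. Excluding patients with a single option does remove the most strongly indicated cases.
- **That a large regression would settle the matter.** With an assumed 17% versus 4% event rate, 90 × 0.17 + 90 × 0.04 ≈ 19 events are expected, too few for a many-covariate outcome model.

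The reply does not answer the core. The article does describe its analysis, in two places, and every component is unadjusted. Disclosing a bias in the limitations does not correct it in the Statistics section, and the Discussion draws stronger conclusions than the limitations section allows.

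**Conclusion.** The point holds as a statement about the analysis this article sets out. Physician choice, a planned comparison against a control arm with a 13-point target, and only unadjusted methods together leave the 30-day comparison open to confounding of unknown size and direction. Dual eligibility does not close that gap.

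Under the main assumed scenarios the spurious difference is 4 to 7.5 points, about a third to somewhat over half of the design effect. A crude two-sided 5% test at 90 per arm would reject in about 10% to 20% of registries with no true effect. At the lower event rates tried, the figures are 2.7 to 5 points and about 8% to 14%. These ranges rest on a single assumed binary factor and assumed risks. They show what is possible and do not estimate the bias in EASE-IT.

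The documents do not support the further inference that the result will be wrong, or that no adjusted analysis exists in a document not shown.

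**What to change.** **Statistics section.** Make the main between-group estimate of the 30-day composite an adjusted risk difference (no BAV minus BAV) with 95% CI. Obtain it by propensity-score overlap weighting or inverse-probability weighting, accounting for centre. Prespecify a short set of admission variables from Table 1, for example risk score, echocardiography, ECG, creatinine and comorbidities. Table 1 does not list LVEF by name, so state which echocardiographic measures are used. Report covariate balance before and after weighting, add a sensitivity analysis for unmeasured confounding such as an E-value, and keep the crude comparison as supportive.

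**Limitations and Discussion.** Confine the eligibility statement to positivity. Describe the result as an adjusted observational comparison with residual confounding, and moderate the conclusions about dropping pre-dilation to match. If no adjusted estimate is adopted, label the comparison descriptive.

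**Cost.** The listed variables are already collected, so the change is one of analysis and wording. Weighting will widen the interval somewhat. With few events any outcome model must stay small, which is why weighting is preferable to a logistic model with many covariates. Since the drivers of the choice are only partly known, adjustment will reduce the problem but cannot be assumed to remove it.

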## Discussion

EASE-IT represents a prospective, multicenter, two-armed registry aimed at documenting the course of patients undergoing TA-TAVI using the Edwards SAPIEN 3 with or without pre-dilation via BAV. Information provided by EASE-IT will be used to assess the value of pre-dilation during TAVI procedures and to investigate associations between patient characteristics and outcomes. Thus, results obtained from the EASE-IT registry should have several important implications.

Although recent pilot studies have preliminarily suggested the feasibility and safety of performing TF-and TA-TAVI without pre-dilation of the stenosed aortic valve [18–20], these studies have not directly compared the outcome of patients undergoing TAVI with and without pre-dilation. Nevertheless, in the study by Grube et al. [18], 60 subjects undergoing TF-TAVI using the MCV device in the absence of BAV were compared to a historical control group (with BAV), suggesting that the efficacy of the simplified procedure (i.e., without pre-dilation) was similar to that of the standard approach. However, it is known that this type of comparison can be associated with several methodological limitations. Therefore, the conclusions by Grube et al. must be appropriately verified. In addition, data regarding delivery of the Edwards SAPIEN THV in the absence of pre-dilation are extremely limited [20]. For these reasons, EASE-IT has been designed to determine whether BAV during TA-TAVI using the Edwards SAPIEN 3 yields relevant beneficial or negative procedural effects based on a two-armed registry approach, which will allow for direct comparison between the patient groups (i.e., with BAV *vs.* without BAV). Thus, the comparative analysis that can be performed from information collected during the EASE-IT registry will be fundamental for establishing the importance of pre-dilation during TA-TAVI.

Notably, a recent imaging study suggested that new silent cerebral lesions appear in approximately 90% of patients undergoing TAVI [21], with the highest number of embolisms shown to occur at the time of pre-dilation and valve deployment [22]. This is interesting considering that BAV has been suggested to cause thrombosis, which can result in coronary obstruction, myocardial infarction, or stroke [16]. In addition, BAV has been linked to transient ischemia (coronary, cerebral, and renal), aortic root rupture, as well as hemodynamic failure and/or systemic inflammation in patients with reduced LVEF [14–16, 23]. With regard to these BAV-related complications, EASE-IT should yield important information concerning the benefit of pre-dilation during TAVI. Indeed, if the results of EASE-IT demonstrate that BAV during TA-TAVI is unnecessary or detrimental, then these risks could be avoided altogether by elimination of the pre-dilation step. On the other hand, if BAV is found to contribute to procedural success, then exposure to these potential BAV-associated risk factors may be warranted. Also, it is possible that BAV will yield differential benefits or procedural risks within distinct populations (e.g., detrimental for patients with reduced LVEF). For this reason, EASE-IT will also examine associations between patient characteristics and outcomes. Thus, results obtained from the EASE-IT registry have the potential to promote evolution of the TAVI procedure in order to reduce the risk of microembolization, stroke, and other severe complications in patients with AS.

Regarding exclusion of the pre-dilation step during TAVI, the resulting simplified approach might reduce the procedural time, amount of contrast agent used, and duration of fluoroscopy as indicated by Wendler et al. [20]. In this regard, as part of the secondary evaluation criteria in EASE-IT, information related to these procedural factors will be recorded for analysis. Indeed, the simplified approach would also eliminate the delay between pre-dilation and valve deployment, which represents a time during which patients can become hemodynamically unstable. Thus, removal of the pre-dilation step has been suggested to be ideal for avoiding complications in patients with severely impaired LVEF [20]. Nevertheless, additional risks may be associated with implantation of the valve in the absence of pre-dilation, such as the potential need for post-procedural dilation, which was found to be required in 16.7% of subjects in the absence of BAV by Grube et al. [18]. Thus, EASE-IT will be important for analyzing the potential benefits or disadvantages associated with altering procedural factors during the simplified TAVI approach.

Furthermore, results obtained by EASE-IT regarding the importance of pre-dilation during TAVI might only be applicable to the Edwards SAPIEN 3, and not other commercially available devices. In this regard, another ongoing prospective, randomized trial has been initiated by a group at Bonn University (NCT01539746; Transcatheter Aortic Valve Implantation Without Pre-dilation [SIMPLIFy TAVI]) in order to investigate the 30-day composite endpoint in patients with severely impaired LVEF (≤35%) undergoing TAVI using MCV devices. Therefore, EASE-IT registry results, which are likely to be reported after completion of the SIMPLIFy TAVI trial (scheduled to end December 2014), should hold particular significance with regard to the generalizability of the impact of BAV on TAVI outcome as related to distinct devices and populations. Indeed, studies testing the importance of the pre-dilation step will need to be carried out for specific delivery systems, routes, and patient populations in order to conclusively determine whether the use of BAV is beneficial. Therefore, EASE-IT will be essential for contributing to the body of data necessary for establishing the value or risk associated with pre-dilation procedures during TAVI.

